### Study logistics

#### Recruitment

Potential participants will initially be approached about the study by any health-care professional who is involved in their care provided that the consultant psychiatrist for the team has agreed in principle that patients under their care may take part in the study.

If a psychiatrist or other health-care professional has a patient under their care who they believe meets the eligibility criteria for the study, they will introduce the patient to the study at an appropriate time by briefly describing it and provide an information sheet. The information sheet will include an explanation of the exact nature of the trial, the requirements of the protocol, any known adverse effects of the trial medicine, and any known risks involved in taking part. It will be clearly stated that the patient is free to withdraw from the trial at any time for any reason without prejudice to future care and with no obligation to give the reason for withdrawal.

The patient must provide verbal agreement to discuss their eligibility and possible enrolment into the trial with a member of the research team before any further step in the study process can take place. If a patient does not give verbal agreement to discuss their eligibility and possible enrolment into the trial, no further aspect of the screening process will be carried out at that time. However, where a patient later decides that they are willing to be considered for entry into the trial, previous refusal does not preclude this. Where verbal agreement is given, the patient will be assigned a screening number and contacted by the research team to discuss consent.

Potential participants will be given no less than 24 h from receiving the information sheet to consider the information and the opportunity to question the investigator, their general practitioner (GP), or other independent parties regarding participation in the trial. Written informed consent then will be obtained and will include permission for the LABILE research team to notify the patient’s GP and consultant (who may be the referring psychiatrist) about the enrolment of their patient into the trial. Additionally, the patient will be asked whether a family member or friend can be contacted solely for the purpose of helping the team to obtain follow-up data, for which a separate written informed consent will be required. The patient will not be excluded from the study if he or she does not give consent for the research team to contact family members or friends. A copy of the signed informed consent form(s) will be given to the patient and their consultant. The original signed form(s) will be retained at the trial site.

#### Screening and baseline

If consent is given and documented, a screening assessment CRF will be completed with the participant. If the participant fulfils the eligibility criteria, they will complete the baseline assessment and be randomly assigned. After randomization, the participant’s GP and consultant will be informed of their enrolment into the trial.

#### Follow-up

The 12-, 24-, and 52-week assessments (Table 1) will be scheduled to coincide with the supplying of the participant’s study medication. Prior to preparing each new prescription, the psychiatrist or researcher will contact the participant to elicit details of any adverse events and to ascertain whether they wish to continue with the trial. If the participant continues to experience adverse event(s), further monitoring will be performed even when they are no longer being prescribed the study medication. Further follow-up by visit or telephone call will be arranged as required. All participants will be offered a £20 honoraria after completion of the 52-week follow-up interview.

### Data management and analysis

Data will be entered onto a secure web-based data entry system. Access will be restricted by user identifiers and passwords (encrypted by using a one-way encryption method). The database will be backed up daily in encrypted form, and offsite copies will be made at regular intervals. Study data will be archived securely and then safely destroyed after 15 years. Analysis and reporting of the trial will be in accordance with CONSORT (Consolidated Standards of Reporting Trials) guidelines. Further details about the statistical analyses will be provided in the statistical analysis plan which will be finalised prior to completion of data collection, database lock, and unblinding of the study.

Continuous variables will be summarised in terms of the mean, SD, median, lower and upper quartiles, minimum, maximum, and number of observations. Categorical variables will be summarised in terms of frequency counts and percentages. Descriptive statistics of demographic and clinical measures will be used to examine balance between the randomized arms at baseline. The primary approach to between-group comparisons will be to analyse participants according to the group to which they were allocated, regardless of treatment received, and without imputation of missing outcome data. All data will be analysed by using Stata version 13 or a later version.

Appropriate descriptive statistics for ZAN-BPD score will be reported for each randomly assigned group at each scheduled follow-up time point. There are two proposed analyses of ZAN-BPD data. For our primary analysis, ZAN-BPD score at 52-week follow-up, randomly assigned groups will be compared by using a generalised linear model for continuous outcome adjusted by baseline ZAN-BPD score, centre, severity of personality disorder (simple or complex), and the extent of bipolarity (score of at least 14 or of less than 14). The effectiveness parameter comparing lamotrigine plus usual care with usual care alone will be the difference in mean ZAN-BPD score at 52 weeks along with 95 % confidence interval and exact *P* value.

For our main secondary analysis, ZAN-BPD scores at 12, 24, and 52 weeks will be compared by using a mixed model for repeated outcome measures adjusted by the same stratification variables used for the primary analysis. We will investigate whether any treatment effects were sustained or emerged later by including an interaction term between treatment group and time in the model. In the absence of a time effect, the effectiveness parameter will be the average difference in mean ZAN-BPD score over the 52-week period along with 95 % confidence interval and exact *P* value.

Sensitivity analyses will be conducted for both analyses (i) to further adjust for any variable with marked imbalance at baseline, (ii) to investigate the impact of missing data by using multiple imputation, and (iii) to investigate the effect of treatment adherence.

Analysis of secondary outcomes will follow a similar approach by using appropriate mixed effects regression models (for example, logistic for binary outcomes) (that is, comparison at both 52-week follow-up and by using repeated measures analysis of follow-up data collected at 12, 26, and 52 weeks).

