### Assessments

The timing and sequence of all assessments are summarised in Table 1*.*

**Table 1 Tab1:** Study assessment schedule

Assessments	Screening	Baseline	12-week follow-up	24-week follow-up	52-week follow-up
Structured Clinical Interview for DSM-IV Axis II Personality disorders	X	-	-	-	-
Structured Clinical Interview for DSM-IV (SCID-I)^a^	X	-	-	-	-
Hypomanic Checklist	X	-	-	-	-
Alcohol, Smoking and Substance Involvement Screening Test (ASSIST)	X	-	-	-	X
Morisky scale	-	-	X	X	X
Zanarini Rating Scale for Borderline Personality Disorder (ZAN-BPD)	-	X	X	X	X
Beck Depression Inventory	-	X	X	X	X
Acts of Deliberate Self Harm	-	X	X	X	X
Social Functioning Scale	-	X	X	X	X
EuroQoL-5D	-	X	X	X	X
Side Effect Scale	-	X	X	X	X
Modified Adult Service User Schedule	-	X	X	X	X

*DSM-IV* Diagnostic and Statistical Manual of Mental Disorders (4th edition), *EuroQoL-5D* European quality of Life-5 dimensions

^a^Section on bipolar affective disorder (type I and II)

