#### Secondary outcomes

Scores on the ZAN-BPD in the 52 weeks after randomization using repeated measures analysis of data collected at 12-, 26-, and 52-week follow-up.Total score on the 21-item Beck Depression Inventory [19] at 12, 24, and 52 weeks. The Beck Depression Inventory has been widely used as a self-completed questionnaire, provides a valid assessment of the severity of depressive symptoms, and can be completed in less than 10 min [20].Incidence and severity of suicidal behaviour, assessed by using the Acts of Deliberate Self-Harm Inventory [21] at 12, 24, and 52 weeks. This structured interview collects detailed information about the number and severity of episodes of self-harm and has been used successfully in other trials of treatments for people with BPD [22].Social functioning, assessed by using the Social Functioning Questionnaire at 12, 24, and 52 weeks. This questionnaire is an eight-item self-report scale that asks people about problems across a range of settings that people with personality disorder often experience [23].Health-related quality of life, assessed by using the EuroQoL-5D (European quality of Life-5 dimensions) [24] at 12, 24, and 52 weeks. The EuroQOL-5D provides a brief and reliable measure of health-related quality of life and is responsive to change in people with BPD [25].Side effects, assessed at 12, 24, and 52 weeks by using a pro forma designed to cover the possible side effects listed in the British National Formulary entry for lamotrigine [26].Use of alcohol and other drugs at 52 weeks, assessed by using the Alcohol, Smoking and Substance Involvement Screening Test (ASSIST) [27]. This short questionnaire provides a reliable and valid screening test for problem substance use [28].Use of concomitant anti-psychotic and other psychotropic medication defined as the proportion of people taking anti-psychotics, anti-depressants, benzodiazepines, and hypnotics 24 and 52 weeks after randomization.Total cost of health and social services; resource use information will be collected at 12, 24, and 52 weeks by using the Adult Service Use Schedule adapted for use in this trial on the basis of previous research involving people with personality disorders [29]. This questionnaire collects detailed data on the use of all hospital and community health and social care services.

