### Assignment of interventions

After consenting to participation and completing screening assessments, patients who are found to be eligible will be randomly allocated to the intervention or comparator arm of the trial by the automated randomization service operated by Nottingham Clinical Trials Unit. Equal numbers of participants will be randomly assigned to each arm of the trial. Stratification will occur by study centre, severity of personality disorder (simple or complex personality disorder according to criteria developed by Tyrer and Johnson [13]), and extent of bipolarity (using a score of more or less than 14 on the Hypomania Checklist [15]).

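### As written, the repeated-measures model of ZAN-BPD adjusts for the stratification variables and does not include baseline ZAN-BPD, which costs precision in the main secondary analysis

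*Protocol article*

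**What the plan says.** The primary model compares 52-week ZAN-BPD between arms, "adjusted by baseline ZAN-BPD score, centre, severity of personality disorder (simple or complex), and the extent of bipolarity" (Data management and analysis). That is four covariates, with the baseline score named first and apart from the other three.

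The next analysis in the same section takes three follow-up occasions as outcomes: "For our main secondary analysis, ZAN-BPD scores at 12, 24, and 52 weeks will be compared". Its covariates are given in one clause: "compared by using a mixed model for repeated outcome measures adjusted by the same stratification variables used for the primary analysis". If there is no time effect, the treatment effect is the average difference over the 52 weeks.

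The stratification variables are defined under Assignment of interventions: "Stratification will occur by study centre, severity of personality disorder", followed by extent of bipolarity. Baseline ZAN-BPD is not among them. Table 1 shows that it is measured before follow-up begins.

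For the remaining outcomes the section says: "Analysis of secondary outcomes will follow a similar approach". It names a 52-week comparison and a repeated-measures analysis, but no covariates.

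**The concern.** The repeated-measures analysis is the first-listed secondary outcome. The Discussion gives it a purpose of its own: the condition fluctuates, so benefit might occur without showing at 52 weeks. A statistician who follows the stated covariate list would fit it without the baseline score. Baseline would not enter as an outcome occasion either, because only the three follow-ups are listed.

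When baseline and follow-up scores are positively correlated, leaving baseline out makes the standard error larger than it need be, and any chance difference between arms at baseline stays in the estimate. The article states no reason for using a different covariate set in the two ZAN-BPD models and no gain from doing so.

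**Working it through.** **1. The covariate sets side by side**

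| Analysis | Stratification variables | Own baseline |
|---|---|---|
| Primary, ZAN-BPD at 52 weeks | yes | yes, named |
| Main secondary, ZAN-BPD at 12, 24 and 52 weeks | yes | not named |
| Costs (Health economic analysis) | yes | yes, named |
| Other secondary outcomes | not stated | not stated |

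Both places that spell out an own-baseline adjustment list it in addition to the stratification variables. In the article's own usage, then, the term does not cover the baseline score.

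**2. The plan's own figure**

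Inputs from Sample size: difference 3.0, SD 6.75, two-sided 0.05, power 90%, loss 15%.

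- n per arm = 2 × (1.960 + 1.282)² × 6.75² / 3.0² = 106.4, so 107 per arm and 214 in total. Power at 107 per arm is 90.2%.
- 214 / (1 − 0.15) = 251.8, so 252.

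Both figures reproduce. Neither relies on baseline adjustment.

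**3. Precision of the averaged difference**

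Let ρ be the correlation between any two follow-ups and r the correlation of baseline with each follow-up. The article gives neither, so both are assumptions. The calculation takes equal correlations, SD 6.75 at every visit and complete data on 107 per arm. It ignores any gain from the stratification factors.

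- Variance of a participant's three-visit mean, in units of SD²: (1 + 2ρ)/3 without baseline, and (1 + 2ρ)/3 − r² with baseline as a covariate.
- SE of the difference = 6.75 × √(variance × 2/107).

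At ρ = 0.6 without baseline, the variance is 2.2/3 = 0.733 and SE = 6.75 × √(0.733 × 2/107) = 0.790. Power is 96.7% for a difference of 3.0 and 71.6% for an illustrative difference of 2.0. With baseline:

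| r | Variance | Reduction | SE | Power at 3.0 | Power at 2.0 |
|---|---|---|---|---|---|
| 0.2 | 0.693 | 5% | 0.768 | 97.4% | 74.0% |
| 0.3 | 0.643 | 12% | 0.740 | 98.2% | 77.1% |
| 0.4 | 0.573 | 22% | 0.699 | 99.0% | 81.7% |
| 0.5 | 0.483 | 34% | 0.642 | 99.7% | 87.6% |
| 0.6 | 0.373 | 49% | 0.564 | over 99.9% | 94.4% |

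At r = 0.5 the 95% interval half-width is 1.96 × 0.790 = 1.55 without baseline and 1.96 × 0.642 = 1.26 with it.

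**4. Sensitivity to ρ**

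At r = 0.4 the variance reduction is 27%, 24%, 22% and 20% for ρ = 0.4, 0.5, 0.6 and 0.7. Power at 3.0 without baseline is 98.7%, 97.8%, 96.7% and 95.3% for the same values.

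**5. Visit labels**

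Table 1 has a 24-week visit and no 26-week visit. Under Secondary outcomes, the ZAN-BPD item is described as "using repeated measures analysis of data collected at 12-, 26-, and 52-week follow-up", while the other outcomes measured at that visit are placed at 24 weeks. Data management and analysis uses 24 weeks for the main secondary analysis and 26 for the other secondary outcomes. The Discussion uses 26.

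**The case against.** The best reply is that the clause is loose shorthand. It points back to the primary analysis, which includes baseline ZAN-BPD, and the article never says that baseline is excluded or that the stratification variables are the only covariates. This stands as far as intent goes: omission may not be what the authors mean. It does not settle the wording, because the article elsewhere lists own-baseline adjustment separately from the stratification variables. If the same set was meant, the sentence still needs correcting.

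Second, the article leaves further detail to a statistical analysis plan to be finalised before unblinding. That plan is not shown and may include baseline. But the article is not silent here. It states a covariate set, and adding detail later is different from changing that set.

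Third, one planned sensitivity analysis adjusts further for any variable with marked baseline imbalance, and it applies to both ZAN-BPD analyses. This protects against a marked imbalance in baseline ZAN-BPD. It does not recover precision in general, since it is triggered only by imbalance.

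Fourth, the practical stakes are limited. This is a secondary analysis, and at the planned difference of 3.0 the averaged comparison has about 95% to 99% power without baseline over the range of ρ shown. That stands, and it keeps the point modest.

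**Conclusion.** The point holds as a matter of stated wording: followed literally, the main secondary model omits a covariate that is collected and that the primary model uses. The cost is precision in the averaged difference. Its size depends on correlations the article does not give, so the 5% to 49% range at ρ = 0.6 is illustrative and not a property of this trial.

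A reader might infer more than the article supports:

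- **Deliberate removal of baseline.** The text does not show this; loose wording is possible.
- **Estimates that cannot be compared.** Under randomization, linear models with and without baseline target the same difference in means. The 52-week estimates can differ through adjustment alone, but the quantity is the same.
- **Omission in every secondary outcome.** The article promises only a similar approach. The 52-week comparisons may follow the baseline-adjusted primary model, so the covariates are unclear, not stated to be absent.
- **A fixed loss from the single-visit formula.** The ratio 1/√(1 − r²) gives a standard error 9%, 15% or 25% larger at r = 0.4, 0.5 or 0.6. It describes one visit, whereas the named parameter is the average over three, which also depends on ρ.

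The 24/26-week mismatch is a clerical matter and adds no weight to the covariate point.

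**What to change.** State that the mixed model for ZAN-BPD uses the same covariates as the primary model: baseline ZAN-BPD, centre, severity of personality disorder and extent of bipolarity. State also that the repeated-measures model for each other secondary outcome adjusts for its own baseline where Table 1 collects one. If omission of baseline is intended, give the reason.

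Separately, reconcile the 24-week and 26-week labels across Table 1, Secondary outcomes, Data management and analysis, and the Discussion.

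The cost is wording only, settled before unblinding. The baseline data are already scheduled, and the sample size does not change.

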#### Health economic analysis

The economic evaluation will take the NHS/Personal Social Services perspective preferred by the National Institute for Health and Clinical Excellence [31] and shown to be the key cost sector in previous research among people with BPD [29]. Data on the use of health and social services will be collected by using a modified version of the Adult Service Use Schedule adapted for use in this population on the basis of previous research in this area [29]. The cost of lamotrigine will be calculated by using the generic cost listed in the British National Formulary and the cost of the time with the dispensing clinician by using national UK unit costs. National UK unit costs will be applied to medication, hospital contacts, and community health and social services [32, 33].

Differences in mean costs will be analysed by using standard parametric *t* tests with the validity of results confirmed by using bias-corrected, non-parametric bootstrapping (repeat re-sampling) [34]. Despite the skewed nature of cost data, this approach is recommended to enable inferences to be made about the arithmetic mean [35]. Cost-effectiveness will be assessed through the calculation of incremental cost-effectiveness ratios [36] and will be explored in terms of cost utility by using quality-adjusted life-years derived from the EuroQoL-5D and cost-effectiveness by using the ZAN-PD. Uncertainty around the cost and effectiveness estimates will be represented by cost-effectiveness acceptability curves [37]. All analyses of cost will be adjusted for baseline stratification variables and baseline costs.

### Data monitoring

The project will be overseen by a trial steering committee (TSC) made up of a representative of the project funder and independent representatives of service users and providers. An Independent Data Monitoring and Ethics Committee will monitor recruitment of study participants, ethical issues of consent, quality of data (including missing data), the incidence of adverse events, and any other factors that might compromise the progress and satisfactory completion of the trial. The group will have access to unblinded data if requested. It will be chaired by an independent academic and report to the TSC.

Day-to-day running of the project will be overseen by a trial management group. The role of the group will be to monitor all aspects of the conduct and progress of the trial, ensure that the protocol is adhered to, and take appropriate action to safeguard participants and the quality of the trial itself. The group will act in accordance with decisions made by the TSC. People with experience using services will be represented on the TSC and contribute to the design, conduct, and reporting of study findings.

### Ethics

Approval for the research was given by the London Central Research Ethics Committee (reference number 12/LO/1514) and by the Research and Development departments of the participating NHS Trusts. We will ensure that the trial is conducted in full conformity with the current revision of the Declaration of Helsinki (last amended October 2000, with additional footnotes added 2002 and 2004) and with the Medicines for Human Use (Clinical Trials) Regulation 2004 transposed into law from the EU Clinical Trials Directive 2001/20/EC, the EU Good Clinical Practice Directive 2005, and all current and future acts and requirements pertaining to its conduct.

Each study participant will be assigned a unique trial identification number at the start of the assessment process. This number will be written on all clinical assessment forms/datasheets and databases used to record data on study participants. A hard copy of a record sheet linking patient identity, contact details, and trial identification number for all participants will be kept at each site. It will be placed in the investigator site file, in a locked filing cabinet, separate from the paper CRFs and other documents relating to a participant, which will be anonymised. Recorded data will be entered onto an electronic data management system that will use the trial identification number rather than the participant’s name or other information that could identify them.

## Discussion

The LABILE trial will be the first study to examine the long-term clinical effectiveness and cost-effectiveness of lamotrigine for people with BPD. As such, the trial has the potential to help guide prescribers and patients when deciding whether this drug could help reduce the distress they experience and improve their quality of life.

Current guidance from the National Institute for Health and Care Excellence states that drug treatments should “not be used for BPD or for the individual symptoms or behaviour associated with the disorder” [38]. This position was endorsed by subsequent guidance issued by the National Health and Medical Research Council in Australia [39] but contrasts with earlier American guidelines which state that mood stabilizers should be considered as a second-line treatment for affective dysregulation in patients with BPD [40]. The need for further trials of pharmacological treatments for people with borderline personality was highlighted in a Cochrane systematic review in 2008 [41]. Previous reports have highlighted the uncertainty that prescribers currently experience when considering whether to use pharmacological approaches to help people with BPD [42], and we believe that this trial can help reduce some of this uncertainty.

Strengths of the LABILE study are that it has a clear primary hypothesis based on an outcome measure which assesses core features of BPD. As BPD is a long-term condition and previous placebo-controlled trials have examined outcomes only over 8 to 12 weeks, we want to examine the longer-term effects of offering people this treatment. For this reason, our primary outcome measure is score on the ZAN-BPD at 52 weeks. However, BPD is also a fluctuating condition, and it is possible that patients may derive some benefit from treatment even if these are not seen at 52 weeks. For this reason, the first of our secondary outcomes is symptoms of BPD over the 52 weeks after randomization using repeated measures analysis of data collected at 12-, 26-, and 52-week follow-up. This measure will allow us to examine whether patients who are offered lamotrigine have improved mental health in the year after they are first offered this treatment.

Other strengths are that we are recruiting participants from a broad range of secondary care mental health services and we have limited our exclusion criteria with the aim of generating findings that are generalisable across the NHS in England and in other countries with similar health-care systems. Finally, the study is collecting detailed information about resource use and other costs that will enable us to conduct a high-quality economic evaluation of the impact of adding lamotrigine to usual care of people with BPD.

This trial faces a number of challenges which will need to be overcome if we are to recruit to target. In addition to pressures of workload and other factors that may deter clinicians from referring people to clinical trials, clinicians may be concerned about the impact of the trial on what can sometimes be strained relationships with patients. National guidance on the treatment of people with BPD in England advises against the use of pharmacological treatments and this may deter some clinicians from referring people to the study. Potential participants may be concerned about being asked to take part in a study in which they might be allocated to an inert placebo for a 12-month period. In an attempt to overcome these obstacles, we have developed information for clinicians that emphasises the extent of off-label prescribing of psychotropic medication for people with personality disorder and reminds them that national guidance is based on the relative absence of evidence rather than evidence of lack of effect. Initial discussions with potential participants suggest that many recognise the limitations of current treatment options and that there is considerable interest in taking part in the study.

We have previously concluded that existing evidence is insufficient to recommend the use of lamotrigine or other mood stabilizers in clinical practice [42]. The LABILE study has the potential to reduce this uncertainty by generating high-quality evidence on the impact of adding this drug to the usual care that patients receive over the course of a 12-month period.

